## Abstract

**Background:**

The transplantation process usually takes place without transplant teams being able to use imaging data to assess graft quality. The decision of whether to go get the graft or not is therefore limited and suboptimal. “Cristal images” is a teleimaging project allowing real-time visualization of images of the organs of the donor. The objective of our study is to assess whether the use of a secure teleimaging can improve the effectiveness and efficiency of the procurement and transplantation processes.

**Methods:**

We will use the exhaustive national registry of organ allocation and transplantation, and compare outcomes before the deployment of “Cristal images” (years 2015–2016) and after it becomes operational (years 2018–2019) for heart, lung, liver and kidney transplant in a before-after study, combined with a preference elicitation study. The primary endpoint will be the number of successful organ transplantations. Secondary endpoints will be related to the efficiency of the transplant process (decision making, transportation, cost) and a preference elicitation study will determine the relative preferences of transplant teams towards few “Cristal images”’ components or potential developments, which are yet to be determined through a qualitative analysis based on interviews with professionals.

**Discussion:**

This study will provide stakeholders data on the efficiency of real-time visualization for transplant teams and identify the levers likely to influence the technology use among these teams.

**Trial registration:**

clinicaltrials.gov: NCT03201224, 13 June 2017, retrospectively registered.

## Background

Organ transplantation is the treatment of choice for patients with terminal organ failure. In France in 2017, organ transplant activity amounted to 5,729 transplants, an increase of nearly 30% since 2006 [1]. However, 16,413 patients remained on the national waiting list for transplantation as of January 1, 2018, and in 2017, 590 patients died while on the waiting list [1]. Improving organ procurement remains a challenge with the increasing age (almost 58 years) and associated co-morbidities of deceased donors resulting in “extended criteria” transplants [1].

The two major steps of the transplant process are 1) the evaluation by the donor procurement teams, and 2) proposal to the transplant teams, according to national allocation rules. Without the possibility of image transmission between the procurement and the transplant teams, decisions are made without any assessment of organ anatomy by the transplant teams. The transplant team accepting the graft will travel to the procurement site to verify the graft aspect. If the graft is ill-suited to their patient’s anatomy, the team has to relinquish the graft, which increases the risk of organ necrosis and loss due to prolonged ischemia.

Teleimaging has been shown to be feasible and reliable for pre-transplant decision support and procurement planning [2–6]. Teleimaging could therefore offer a solution to reduce the risk of non-procurement by allowing the transplant team to accept or not a graft after examining high quality images. “Cristal Images” is a teleimaging project funded by the French ministry of health to upload radiological images on local site to a server for remote visualization in streaming. Its objective is to make images of donor organs available to the transplant team early in the transplantation process, anonymously and securely.

## Methods/design

### Study design

We will evaluate “Cristal Images” by conducting a mixed-methods study involving an effectiveness study focusing on the processes and outcomes, and a preference elicitation study focusing on the perception of the transplant teams.

### Aim & setting

Our objective is to assess whether the use of a secure image transmission in the context of organ transplantation can improve the effectiveness and efficiency of the transplantation process and change the practice of the procurement and transplant teams.

### Effectiveness study

#### Participants and data source

Our data will be provided by an extraction of the national registry of transplantation. This registry is exhaustive, collects all relevant clinical data regarding the donor and the recipient, such as age, cause of death, organ status. It also collects process data, such as number of transplant teams contacted, time between organ procurement and transplantation.

#### Inclusion criteria

Organs from a brain-dead donor among: kidney, liver, heart and lung.Donor age over 18Deceased in France

#### Non-inclusion criteria

Organs of a patient deceased after a cardiac arrest (Maastricht Classification: Type II and III) [7]Organs of a patient deceased in French overseas territories

#### Design

We designed an uncontrolled before/after study. Ethically, it was not possible to use any prospective control group, as the underlying hypothesis for the deployment of teleimaging was that it could only benefit recipients and therefore equipoise was impossible if image transfer were made unavailable in some regions.

The “before” period ranged from 2015/01/01 to 2016/12/31 when the “Cristal Images” image transfer platform was unavailable, and the “after” period ranged from 2018/01/01 to 2019/12/31. The intermediate period will not be taken into account as it is a period of deployment, tests, debugging, and adoption of the new technology.

#### Endpoints

##### Primary endpoint

Graft survival rate, assessed clinically and biologically 3 months after surgery for kidney, and 1 year after surgery for liver, heart and lung.

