#### Statistical analyses

##### Sample size

In 2015, there were a total of 5746 transplants from deceased donors (heart: *n* = 471; lung: *n* = 345; liver: *n* = 1355; kidney: *n* = 2939). 335 (15.4%) vital organs (heart, lung, liver) proposed to transplant teams were finally not transplanted. 297 (10.1%) kidneys were collected but not transplanted.

Our hypothesis is that image transfer will reduce lost organs by 82 (11.6%) for vital organs (heart = 20, lung = 17, liver = 45) and about 100 (6%) for kidney.

With a probability of Type I Error of 0.05 and a Power a 90%, the sample size required is 1797 vital organs transplantations and 924 kidney transplantations, which is inferior to our estimated cohort size of deceased donors.

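### The primary endpoint is a count in the abstract and a post-surgery graft survival rate in the endpoint section, while the 90% power is calculated for a third quantity, organs lost before transplantation

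*Protocol article*

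**What the plan says.** The protocol article describes its main outcome in four places.

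- **Abstract, Methods:** "The primary endpoint will be the number of successful organ transplantations". Success is not defined and no denominator is given.
- **The section on the primary endpoint:** here the outcome is a rate, worded as "Graft survival rate, assessed clinically and biologically 3 months after surgery for kidney, and 1 year after surgery for liver, heart and lung". The denominator is not written. Because assessment is timed from surgery, the natural reading is transplanted grafts.
- **Sample size:** the baselines are "335 (15.4%) vital organs (heart, lung, liver) proposed to transplant teams were finally not transplanted" and "297 (10.1%) kidneys were collected but not transplanted". The target is "Our hypothesis is that image transfer will reduce lost organs by 82 (11.6%) for vital organs" and "about 100 (6%) for kidney". The calculation is introduced by "With a probability of Type I Error of 0.05 and a Power a 90" percent, and requires 1797 vital organs and 924 kidneys.
- **Type of analyses:** the outcome singled out for modelling is one-year overall mortality, by mixed-effects logistic regression. Other binary variables are to be handled the same way.

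The Secondary endpoints section also lists mortality or loss of graft function at the same time points. That is close to the complement of the stated primary endpoint.

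**The concern.** These are different quantities. If success means a graft surviving at the stated time point, the count equals the number of transplants multiplied by the survival rate, so the two still differ. Organ loss before transplantation is a third quantity, and one-year mortality a fourth.

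Two things are at stake. First, the power statement has to belong to the endpoint that will be tested. Second, teleimaging is meant to act on whether an organ ends up transplanted, and a rate computed only among transplanted organs conditions on that step. The count responds to it, but also moves with the number of donors, which the image platform does not change. In an uncontrolled before/after study, leaving the choice open also allows it to be settled after the data are seen.

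**Working it through.** **1. Which quantity the sample size is for.** Inputs from Sample size: 471 + 345 + 1355 = 2,171 vital organs; 335/2,171 = 15.4% lost; (335 − 82)/2,171 = 11.65%, so the printed 11.6% works as the rate after deployment. Kidney: 297/2,939 = 10.1% lost, with 6% printed as the rate after deployment.

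Formula (two proportions, pooled variance, two-sided 0.05, power 90%, equal periods), with d = p1 − p2 and p̄ their mean:

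n = [1.960·√(2p̄(1−p̄)) + 1.282·√(p1(1−p1) + p2(1−p2))]² / d²

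| Comparison | n per period | With continuity correction | Stated |
|---|---|---|---|
| Kidney, 10.1% vs 6% | 924 | 972 | 924 |
| Vital, 15.4% vs 11.6% | 1,698 | 1,750 | 1797 |
| Vital, 15.4% vs 11.65% | 1,746 | 1,799 | 1797 |

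The kidney figure matches exactly and the vital-organ figure matches closely. Both are numbers per period, not totals. The powered quantity is the proportion of organs lost. No graft survival rate and no effect on graft survival appears anywhere in the document.

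**2. How the survival rate responds to the hypothesised benefit.** Let T be current transplants, R rescued organs, s0 survival of current grafts and s1 survival of rescued grafts.

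- Count: T·s0 + R·s1
- Rate: (T·s0 + R·s1)/(T + R)
- Change in rate: R·(s1 − s0)/(T + R)

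For vital organs T = 2,171 and R = 82, so T + R = 2,253. Survival values are assumptions.

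| s0 | s1 | Count per year | Change in rate (points) |
|---|---|---|---|
| 80% | 70% | 1,737 → 1,794 | −0.36 (80.0% → 79.6%) |
| 80% | 80% | 1,737 → 1,802 | 0 |
| 80% | 100% | 1,737 → 1,819 | +0.73 |
| 95% | 85% | 2,062 → 2,132 | −0.36 |
| 95% | 100% | 2,062 → 2,144 | +0.18 |

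With s1 anywhere from 5 to 30 points below s0, the rate falls by 0.18 to 1.09 points. Kidney (T = 2,939, R = 100) behaves alike: a fall of 0.16 to 0.99 points over the same gaps, and a rise of at most 0.66 points if all rescued grafts survive at s0 = 80%.

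For scale, 90% power for a 2-point gain from 80% needs 8,084 grafts per period. Two years supply about 2 × 2,171 = 4,342 vital organs, and the most that rescue alone can produce is 0.73 points.

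**3. Power for an endpoint that covers both steps.** Take organs proposed per year as 2,171 + 335 = 2,506, hence 5,012 per two-year period, with the same number in each period and no allowance for clustering. Then p1 = 2,171·s0/2,506 and p2 = (2,171·s0 + 82·s1)/2,506.

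Power = Φ{[d√N − 1.960·√(2p̄(1−p̄))] / √(p1(1−p1) + p2(1−p2))}, where d = p2 − p1 and N = 5,012.

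| s0 | s1 | p1 → p2 | Power |
|---|---|---|---|
| 75% | 65% | 65.0% → 67.1% | 61% |
| 75% | 75% | 65.0% → 67.4% | 74% |
| 80% | 70% | 69.3% → 71.6% | 71% |
| 80% | 80% | 69.3% → 71.9% | 82% |
| 85% | 75% | 73.6% → 76.1% | 81% |
| 85% | 85% | 73.6% → 76.4% | 90% |

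**The case against.** The best defence is that graft survival is a legitimate effectiveness outcome. The Background attributes avoidable loss to anatomical mismatch found on arrival and to prolonged ischemia, not to intrinsically poor organs. Better matching and shorter ischemia could raise survival in all grafts, not only add rescued ones. Process losses and extended criteria donors are already secondary endpoints, so added refusals or a shift in case mix would be visible. This much stands: a survival gain across all grafts is possible, and step 2 isolates only the effect of rescuing organs.

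A reader might infer that the count and the rate will point in opposite directions, so that the same data would be called a success and a failure. The documents do not support that. The divergence requires rescued grafts to survive less well. Extended criteria donors appear as a general trend and a secondary endpoint, and nothing says rescued organs come from them. Even in the 80%/70% example neither result would be significant over two years per period. The count goes from 3,474 to 3,588 (Poisson z = 1.37, p = 0.17) and the rate changes by −0.36 points (z = −0.43, p = 0.67).

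None of this reconciles the sections. Secondary endpoints do not settle which quantity is primary, and a possible survival benefit does not supply the missing effect size and power for it.

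**Conclusion.** The concern holds. The article states two different primary endpoints, sizes the study on a third quantity, and names a fourth as its modelled outcome. The stated 90% power applies to neither stated primary. This part rests on the text and on the reproduced sample size, with no outside assumption.

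That a rate conditional on transplantation is nearly blind to the hypothesised benefit rests on the protocol's own 82 and 2,171, on reading the denominator as transplanted grafts, and on assumed baseline survival of 80–95%. The rate is unchanged at equal survival, falls slightly if rescued grafts do worse, and rises by less than 1 point if all survive. The direction is a possibility, not a prediction.

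**What to change.** State one primary endpoint in the abstract, Primary endpoint, Sample size and Type of analyses sections: the proportion of eligible organs that are transplanted and functioning at 3 months (kidney) or 1 year (heart, lung, liver), counting non-transplanted organs as failures. Eligible organs would be those proposed for heart, lung and liver and those collected for kidney, matching the Sample size baselines. Keep graft survival among transplanted organs as a key secondary endpoint, report the raw count descriptively, and analyse the primary with the mixed-effects logistic regression already planned.

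The costs are these.

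- **Power.** It must be restated and will be below the advertised 90% in most scenarios. For vital organs it is about 71% to 82% at 80% baseline graft survival with rescued grafts at 70% to 80%, and about 61% to 90% across 75–85% baseline survival with rescued grafts 0 to 10 points lower. Kidney needs its own calculation.
- **Denominator.** The 2,506 is an assumption. The printed 15.4% is 335/2,171, whereas 335/2,506 is 13.4%. The sponsor should say which is meant.
- **Model.** The planned recipient term has no value for an organ never transplanted, so the primary model needs donor and organ covariates.

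If the sponsor prefers organ loss as primary, the abstract and Primary endpoint sections should say so. The existing sample size then applies, read as per period.

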##### Secondary endpoints

Percentage of organs allocated but not collectedPercentage of graft transportation without transplantPercentage of transplant team travel without organ collectionMortality or loss of graft function, 3 months after surgery for kidney and 1 year after transplantation for the other organsNumber (Percentage) of extended criteria donorsCost of the transplantation process, by a microcosting approach, from the acceptance of the organ by phone by the medical transplant team until the transplantation.Proportion of image transmission by the transplant team during the procurement process

#### Statistical analyses

##### Sample size

In 2015, there were a total of 5746 transplants from deceased donors (heart: *n* = 471; lung: *n* = 345; liver: *n* = 1355; kidney: *n* = 2939). 335 (15.4%) vital organs (heart, lung, liver) proposed to transplant teams were finally not transplanted. 297 (10.1%) kidneys were collected but not transplanted.

Our hypothesis is that image transfer will reduce lost organs by 82 (11.6%) for vital organs (heart = 20, lung = 17, liver = 45) and about 100 (6%) for kidney.

With a probability of Type I Error of 0.05 and a Power a 90%, the sample size required is 1797 vital organs transplantations and 924 kidney transplantations, which is inferior to our estimated cohort size of deceased donors.

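### The 90% power and the sizes 1797 and 924 were calculated for organs lost before transplantation, not for graft survival, the primary endpoint in the Methods; power for graft survival is unstated

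*Protocol article*

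**What the plan says.** The Primary endpoint section of the Methods defines: "Graft survival rate, assessed clinically and biologically 3 months after surgery for kidney, and 1 year after surgery for liver, heart and lung". The Abstract has a different definition: "The primary endpoint will be the number of successful organ transplantations".

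The Sample size section starts from two loss rates observed in 2015: "335 (15.4%) vital organs (heart, lung, liver) proposed to transplant teams were finally not transplanted" and "297 (10.1%) kidneys were collected but not transplanted". Its hypothesis is that image transfer cuts lost organs by 82 for heart, lung and liver together, and by about 100 for kidney. It then concludes: "With a probability of Type I Error of 0.05 and a Power a 90%, the sample size required is 1797 vital organs transplantations", with 924 for kidney, and notes that the expected cohort is larger than this.

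Organ loss appears among the secondary endpoints. The first one listed begins "Percentage of organs allocated but not" and concerns collection; the next concerns grafts transported without being transplanted.

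**The concern.** A sample size justifies a study only for the quantity it was computed on. Here that quantity is the share of proposed or collected organs that never reach a recipient. Such an organ has no graft survival, so it does not enter the denominator of the Methods' primary endpoint at all. Reducing loss changes how many grafts are followed; it does not by itself imply any particular change in their survival rate.

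If the text stays as it is, a null result on graft survival could be presented as coming from a study with 90% power, although no power was ever calculated for that endpoint. The cohort is fixed by calendar (2015–2016 and 2018–2019), so what the primary endpoint can detect is already largely settled and should be stated.

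**Working it through.** **1. Reproducing the plan's figures.** Two-sided alpha 0.05, power 0.90, two proportions with pooled variance and no continuity correction, n per period:

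n = [1.960·√(2p̄(1−p̄)) + 1.2816·√(p₁(1−p₁)+p₂(1−p₂))]² / (p₁−p₂)²

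- Vital organs: p₁ = 335/2171 = 15.4%, where 2171 = 471 + 345 + 1355. After the reduction, (335−82)/2171 = 11.65%, taken as 11.7%. n = (0.9487 + 0.6194)²/0.037² = 1796.1, so **1797**.
- Kidney: p₁ = 297/2939 = 10.1%, p₂ = 6%. n = (0.7541 + 0.4917)²/0.041² = 923.3, so **924**.

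Both match exactly. The article states neither sidedness nor whether the sizes are per period; the match settles both. Two side observations: the printed 11.6% would give 1698 rather than 1797, and 100 fewer lost kidneys gives 197/2939 = 6.7% rather than 6%, which needs about 1,400 per period. Neither exceeds the available cohort.

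**2. What the article gives for graft survival.** No baseline rate, no expected change, and no survival for the additional grafts. No single power figure can therefore be derived from it.

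**3. Illustration.** All of the following are assumptions: the rescued organs are the only mechanism, all of them survive, other grafts are unchanged, and each period holds two years at 2015 volume (2 × 2171 = 4,342 vital organs; 2 × 2939 = 5,878 kidneys). Power is Φ(z−1.96) + Φ(−z−1.96), with z the difference over its standard error.

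- Vital, baseline 80%: (0.80×2171 + 82)/2253 = 80.73%. Difference 0.73 points, standard error 0.853 points, z = 0.854, power 0.134 + 0.002 = 13.7%.
- Kidney, baseline 95%: (0.95×2939 + 100)/3039 = 95.16%. Difference 0.16 points, standard error 0.399 points, z = 0.412, power 0.061 + 0.009 = 7.0%.

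| Organ group | Assumed baseline survival | Power | Smallest difference for 90% power |
|---|---|---|---|
| Vital | 75% | 17% | 3.0 points |
| Vital | 80% | 14% | 2.7 points |
| Vital | 85% | 11% | 2.4 points |
| Kidney | 92% | 8% | 1.5 points |
| Kidney | 95% | 7% | 1.2 points |
| Kidney | 97% | 6% | 0.9 points |

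The last column does not depend on how survival might improve. It solves the formula in step 1 for the difference at n = 4,342 or 5,878.

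**4. Changing the survival of rescued grafts.** If it equals that of other grafts, there is no difference to detect and the rejection rate is alpha, 5%. If it is 30 points lower, the test rejects in 22–39% of studies for vital organs (baseline 75–90%) and 42–84% for kidney (baseline 90–97%), but in the direction of deterioration.

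**5. Counting success per organ proposed or collected.** Survival is again assumed, and so is the denominator.

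- Vital, survival 80%, with 2171 as the denominator, as in the plan's 15.4%: 0.80×1836/2171 = 67.7% vs 0.80×1918/2171 = 70.7%, n = 4,342, power 86%.
- Vital, survival 80%, with 2171 + 335 = 2506 as the denominator: 69.3% vs 71.9%, n = 5,012, power 82%.
- Over survival 75–85% and both denominators, vital organs have about 74–92%.
- Kidney at survival 90% or higher has about 99% or more.

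**The case against.** A reader might infer that the plan's own hypothesis leaves the primary endpoint with power of roughly 5–17%, so that the study is close to powerless. The article does not support this. It hypothesises fewer lost organs and nothing about survival after transplantation. The low figures need a baseline survival and a survival for rescued grafts, and the article gives neither. They also assume that rescued organs are the only route to benefit; better matching of graft to recipient could act on all grafts, and a gain of 2.4–3.0 points (vital) or 0.9–1.5 points (kidney) would be detectable. The 5% at equal survival is alpha, not power. The higher rejection rates when rescued grafts do worse show that low power is one scenario, but they are power to detect harm and do not restore the 90%.

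The second objection is stronger. The Abstract's number of successful transplantations is much closer to organ loss, and if success is counted per organ proposed or collected, power over the full cohort is fairly good. This stands as a reason to settle first which endpoint is primary. It does not carry the 90% over, because that definition also includes post-transplant survival, which the calculation leaves out.

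Finally, an exhaustive registry over fixed years would not recruit differently whatever the calculation said. That is true, and it limits the consequence to what is claimed. Nor is this a detail cut from a condensed article: the article does give a calculation, but for a different quantity.

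**Conclusion.** The point holds in this form: the stated 90% power, 1797 and 924 belong to organ loss before transplantation, and graft survival has no sample size justification in the article. This rests on exact reproduction of both printed figures and needs no assumption beyond the standard two-proportion formula. Power for graft survival is unknown and may be far below 90%. The illustrative 11–17% (vital) and 6–8% (kidney) hold only under the assumptions listed in the working and should not be quoted as properties of the plan. It is an inconsistency between endpoint and calculation, compounded by two definitions of the primary endpoint, and should be corrected before results are interpreted.

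**What to change.** 1. Reconcile the Abstract and the Primary endpoint section so that one primary endpoint is named, with its denominator (grafts transplanted, or organs proposed or collected).
2. In the Sample size section, state that 1797 and 924 are per period, two-sided, and apply to organ loss. Print the rates actually used (11.7% rather than 11.6%; 6% or 6.7% for kidney).
3. For the endpoint chosen, report power or the smallest detectable difference on the full two-year cohorts, separately for vital organs and kidney, with the assumed survival and its source.

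The cost is recalculation and rewording, with no additional patients or data. The stated power may become less favourable, particularly if graft survival among transplanted organs is kept as primary.
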